### Study aims and hypotheses

The hypothesis of this project is that self-administered RA will result in improvements in measures of PCRF, quality of life, and sleep quality, compared to SA and standard of care. To assess this hypothesis, our primary aim is to examine the effect of 6-weeks of RA compared to a regimen of SA or standard of care on fatigue as assessed by:

A. weekly self-report using the Brief Fatigue Inventory (BFI), our primary outcome.

B. objective daytime physical activity on a wrist worn accelerometer using average activity counts/minute.

C. fatigue severity assessed 4 times daily using a visual analog scale recorded on wrist-worn accelerometer.

D. quality of life as assessed by Long Term Quality of Life Instrument (LTQL).

Our secondary aims include investigating the effect of 6-weeks of RA compared to a regimen of SA or standard of care on sleep quality of BC survivors as assessed by:

A. monthly self-report using the Pittsburgh Sleep Quality Index (PSQI), our primary outcome.

B. daily sleep/wake diaries and nighttime actigraphy.

C. examining the relationships between improvements in sleep quality and improvements in quality of life for SA and RA, as assessed by LTQL.

Our other secondary aim is to assess activity parameters required for implementation of an acupressure treatment in a clinical setting including the time to onset of a clinically meaningful effect as well as the duration of effect following cessation of the intervention. These factors are currently unknown for acupressure.

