One of the most widely used sleep measures is the PSQI, which shall be administered at baseline, week 6 and week 10. We shall follow the scoring convention followed for PSQI which constructs scores for seven components, namely sleep quality; sleep latency; sleep duration; habitual sleep efficiency; sleep disturbances; use of sleep-promoting medication; and daytime dysfunction, all derived from the original PSQI. The component scores are summed to obtain a total score, the primary outcome for the proposed study. The modeling framework and subsequent analysis will be similar to that for BFI with the phase variable replaced by a continuous week variable. A logistic regression analysis will be carried out with a dichotomous outcome indicating whether PSQI > 7 or not since the threshold of 7 is considered an indicator for sleep quality in BC survivors. A number of secondary sleep outcomes will be obtained using a conjunction of the Actiwatch-S-S data and sleep diary. These will include measures of total sleep time (minutes spent asleep each night) and sleep efficiency (total sleep time/time in bed* 100). These can all be analyzed using the models and methods described above within the mixed linear or logistic regression modeling framework as appropriate.

2. Assessing differences in time to onset and time to relapse (after treatment ends) across the acupressure arms

Time to onset of the acupressure effect will be investigated by studying the treatment subgroups, namely RA and SA. For fatigue, we shall use the daily average values of VAS-F. Time to onset will be calculated as the first time (in days) the VAS falls down by 3 points in comparison to the baseline. We shall restrict this analyses to subjects whose baseline VAS-F is at least 3. A proportional hazards regression model will be employed to analyze the time to onset data. Treatment arm (RA vs. SA) will be used as the primary covariate in the analysis. Independent variables used in the earlier regression analyses for the primary and secondary aim 1 will be used as additional covariates.

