For sleep, we shall use the VAS-SQ measure to carry out our time to onset analysis. As in the case of fatigue, a 3-point drop from baseline in VAS-SQ for the first time will be considered as onset. Since the VAS-SQ measures are weekly, we shall employ a *discrete survival analysis* technique to analyze this data. A discrete survival model is a logistic regression model of the discrete-time hazards, and is easily implemented in most standard statistical softwares. As in the case for VAS-F, this analysis will be confined to subjects with a baseline VAS-SQ score of 3 or more.

We would analyze similarly the time to relapse since the end of treatment, which is defined as the first time a 3-point increase (VAS-F or VAS-SQ) from the six-week value, occurs. This part of the analysis will be restricted to subjects for whom an onset has occurred.

All statistical analyses will be carried out in SAS 9.3 and PASW version 19.

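### Time to relapse admits any woman who ever had an onset and counts a 3-point rise from her week-6 value without requiring response at week 6, so it does not measure duration of effect after acupressure stops

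*Protocol article*

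**What the plan says.** The section Study aims and hypotheses names, as part of a secondary aim, "the duration of effect following cessation of the intervention". The definitions are in Statistics and power analysis, under the second secondary aim.

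- **Onset, fatigue:** "Time to onset will be calculated as the first time (in days) the VAS falls down by 3 points in comparison to the baseline". This uses daily VAS-F averages and is limited by baseline level: "We shall restrict this analyses to subjects whose baseline VAS-F is at least 3".
- **Onset, sleep:** "a 3-point drop from baseline in VAS-SQ for the first time will be considered as onset". VAS-SQ is described as weekly, with the same minimum baseline score.
- **Relapse:** the clock starts at the end of treatment, and the event is "the first time a 3-point increase (VAS-F or VAS-SQ) from the six-week value, occurs".
- **Who is analysed:** "This part of the analysis will be restricted to subjects for whom an onset has occurred".
- **Model:** relapse is handled like onset ("We would analyze similarly the time to relapse since the end of treatment"), that is, proportional hazards for VAS-F and a discrete-time model for VAS-SQ. The comparison is relaxation (RA) against stimulating acupressure (SA).

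Follow-up for relapse is the 4 weeks after Visit 4. Nothing requires an onset to be sustained or to be still present at week 6.

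**The concern.** The time to loss of an effect can be observed only in someone who still has the effect when the clock starts. Here entry depends on having crossed a line once in the preceding six weeks. The event is measured up from wherever the woman happens to be at week 6, not against the level at which her effect would be gone.

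Three kinds of women enter without a full response at week 6: those who responded and lost it during treatment, those with a partial response, and those whose onset was one low day. For all of them, a return to baseline is not an event. The resulting curve would be read as how long the benefit lasts, which the article presents as needed for clinical use. The RA-versus-SA contrast would carry any difference between arms in how many such women enter.

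**Working it through.** The article gives no relapse rate, event count or power for this analysis, so there is no figure to reproduce.

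**Step 1. Logic of the definitions (no assumed numbers).** Let B be baseline and W the six-week value. The relapse threshold is W + 3. It exceeds B exactly when W > B - 3, that is, whenever the woman is not in response at week 6.

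- B = 6, one day at 3 in week 2 (onset), W = 5.5: the threshold is 8.5, which is 2.5 points above baseline. A return to 6 is censored as relapse-free.
- VAS-F runs from 0 to 10 (Subjective study measures). Relapse needs W + 3 ≤ 10, so it is impossible when W > 7.

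**Step 2. How common this could be (assumed inputs).** The Discussion calls fatigue highly variable within and between participants but gives no SD. Assumptions: baseline VAS-F mean 5.5, SD 1.5; mean on-treatment drop 1, 2 or 3 points, between-woman SD 1.2, building up over 14 days and then constant; day-to-day SD 0.8 to 1.6, autocorrelation 0.4; 7 baseline, 42 treatment and 28 follow-up days; 40,000 women per setting. Among women with an onset:

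| Mean drop | Not in response, week-6 day | Not in response, last-7-day mean | Effect vanishes at once, yet scored relapse-free |
|---|---|---|---|
| 1 | 76-78% | 82-86% | 28-31% |
| 2 | 62-65% | 66-71% | 16-19% |
| 3 | 43-48% | 44-50% | 8-9% |

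No woman in this model loses her response before week 6, so columns 2 and 3 reflect partial response and day-to-day noise. Women within 1 point of baseline on the week-6 day are 4-13% (SD 0.8) or 16-41% (SD 1.6) of those with an onset. Women above 7 on that day are 1-3% or 4-13%.

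**Step 3. The opposite error.** If the effect persists fully through follow-up, the written rule with a single-day reference still scores 4-6% (SD 0.8) or 49-51% (SD 1.6) as relapsed.

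**Step 4. Adding true early loss.** A second model assumes 40% non-responders, 20% who relapse after week 6, 20% durable and 20% who lose response before week 6, with a 4-point effect and day SD 0.5 to 1.5. Of women with an onset, 34-62% are not in response at week 6. Of these, 57% to nearly 100% are scored relapse-free, against 19-51% of those in response.

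**Step 5. Effect on RA versus SA.** Suppose 50% of week-6 responders relapse in both arms. Let q be the share of the risk set not in response at week 6 and r their scored relapse rate. Then p = (1 - q) × 0.50 + q × r, and HR ≈ ln(1 - p_B)/ln(1 - p_A).

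- q = 0.10 v 0.30, r = 0.05: p = 0.455 v 0.365, HR = ln(0.635)/ln(0.545) = 0.75. With r = 0, HR = 0.72.
- q = 0.10 v 0.50, r = 0.05: p = 0.455 v 0.275, HR = 0.53. With r = 0, HR = 0.48.
- q = 0.10 v 0.30, r = 0.43 (the noisy end of step 4, 100% - 57%): p = 0.493 v 0.479, HR = ln(0.521)/ln(0.507) = 0.96.

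The distortion can thus be large or nearly nil, depending on noise and on a difference between arms that the article does not state.

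**Step 6. The corrected rule.** Let M be the mean VAS-F over the last 7 treatment days. Entry requires M ≤ B - 3, so the threshold M + 3 ≤ B. A return above baseline is no longer needed. Under the step 2 assumptions, with the event taken as a 7-day mean at least 3 points above M, the rule flags 87-98% when the effect vanishes and 0-10% when it fully persists.

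**The case against.** A rise of stated size from the end-of-treatment value is a defensible definition of worsening after stopping, and 3 points matches the onset criterion. That stands, and the fix keeps it. What it does not justify is applying the rule to women with no full response left to lose.

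Three stronger readings are tempting, and none is supported.

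- **That 43-78% of women with an onset have lost their response by week 6.** The model behind those figures contains no early loss, and a woman 2.9 points below baseline is counted among them.
- **That the rule overstates duration, or reverses the RA-versus-SA hazard ratio.** Two errors run in opposite directions (steps 2 and 3). A distorted contrast also needs the arms to differ in week-6 response, for which the article gives no figure.
- **That relapse should instead mean no longer being 3 points below baseline.** A woman 3.1 points below baseline would then relapse on a 0.2-point change. With the effect fully retained, that rule labels 35-83% of women as relapsed under the step 2 assumptions.

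It could also be said that such detail belongs in an analysis plan. Here the article itself fixes the event, the reference value and the risk set.

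**Conclusion.** The point holds as a mismatch between the stated aim and the defined analysis. It follows from the wording alone: any woman less than 3 points below baseline at week 6 has a relapse threshold above her baseline and can lose all remaining benefit without an event. Above 7 on VAS-F, the event cannot occur.

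The mismatch is probably not rare, given the variability that the article describes, but every percentage above rests on assumed inputs and shows plausible size only. Neither the net direction of the bias nor its effect on the RA-versus-SA comparison can be determined from the article. The point affects one secondary aim in the two acupressure arms and leaves the primary BFI analysis untouched. It should be corrected before the relapse analysis is run.

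**What to change.** 1. Restrict the relapse risk set to women still at least 3 points below baseline at the end of treatment. For VAS-F use the mean of the last 7 treatment days; for the weekly VAS-SQ use the week-6 score.
2. Keep the 3-point rise as the event. For VAS-F, measure it as a 7-day mean against that end-of-treatment 7-day mean, so that the threshold lies at or below baseline and one bad day does not trigger it. For VAS-SQ the entry restriction applies, but weekly scores allow no such averaging, so false relapses from noise remain possible.
3. Report the proportion in response at week 6 by arm beside the relapse curve, and say that this subset is selected after randomisation.

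The cost is a change of analysis wording, with no new data collection, and a smaller risk set. Under the step 2 assumptions, 14-18%, 29-34% and 50-56% of women with an onset would remain for mean drops of 1, 2 and 3 points (100% minus the third column of the table).

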#### Power analysis

Our power analysis is based on our primary aim of comparing fatigue as measured by BFI across the three study arms.

We compute the power via simulation using a mixed effects model with a between-subject factor group (3 levels), a within-subject factor phase (2 levels), group*phase interaction and a random subject effect. The mean BFI values at mid-treatment were assumed to be 4, 3, 3, respectively for standard care, SA and RA arms whereas the means were taken to be 4, 3, 2 at the end-treatment point in the same arms. The between-subject variance is assumed to be 4 at all time-points whereas the variance of the random subject component is taken to be 4 also (yielding an intra-class correlation of 0.5). These assumed values are estimates based on our pilot data. For this configuration, the power for detecting the difference between groups is more than 0.95 and the power for detecting a significant phase*group interaction is 0.82 with a sample size of 100 per treatment arm and a 5% level of significance. In the second model discussed in the analysis section with phase comprising of end-treatment and washout, if we assume the washout point BFI values to be 5, 4, 3, in the standard care, SA, and RA arms, respectively, the power for detecting either the phase effect or group effect are both around 99%.

We also have powered the study to allow us to observe differences in sleep parameters. The extent of overlap between fatigue and sleep disturbances in BC survivors is currently unknown. Research indicates that 51% of BC survivors experience sleep disruptions and 19% meet diagnostic criteria for insomnia
[35]. While fatigued women are most likely enriched with individuals experiencing sleep disturbances we will conservatively assume that roughly 51% women will have some significant sleep disturbances and 19% will have insomnia per treatment arm. As such, with 100 women per treatment group we will be overpowered for detecting a difference in fatigue and sufficiently powered to detect changes in key sleep measures. For example, using the PSQI as a basis for powering differences in sleep quality from previous studies the mean PSQI in BC patients ranges from 6.84 ± 0.376 to 7.16 ± 0.325.(60,74) A 1 point decrease in the PSQI from ~7 to ~6 is considered clinically significant in this population
[33]. The mean PSQI values at mid-treatment are assumed to be 7, 6, 6, respectively in standard care, SA and RA arms whereas the means are taken to be 7, 6, 5 at the end-treatment point in the same arms. Assuming an intra-subject correlation of 0.5, we have powers above 99% to detect any of the group, phase, and group*phase interaction effects with a sample size of 100 per treatment arm and a 5% level of significance.

All power calculations are carried out on the basis of 100 simulations in the software PASS 2008 (NCSS, Kaysville, Utah, USA).

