### Randomization, blinding and allocation concealment

This is a single-blinded study. Participants, investigators, study nurses and all study staff are blinded. However, the nurses who teach the acupressure will know if participants are assigned to the standard of care arm or one of the two acupressure arms. The randomization scheme was created by the study statistician. Within each county under study, eligible patients are being randomized into one of these three groups: RA, SA or standard of care in a 1:1:1 ratio for a target total of 375 patients.

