## Statistical issues

### Statistics and power analysis

Primary Aim: The primary aim of this study is to investigate the differential effects of different modes of acupressure on fatigue in breast cancer survivors. For this, we are focusing on three fatigue outcomes, namely, BFI, which will be administered weekly, a measure of average daily physical activity and a self-reported fatigue score, both based on Actiwatch-S data. A BFI is collected weekly and provides a measure of average degree of fatigue, a score that ranges between 0 and 10, with higher numbers indicating more fatigue. We will be analyzing the BFI outcome over phases. The first phase BFI is obtained by averaging week-1 to week-3 measures (mid-treatment). The second phase comprising of week-4 to week-6 measures indicates the status in the second half of the treatment phase (end-treatment). The final phase comprises of week-7 to week-10, the washout phase (washout). In order to investigate the change in BFI between the three study arms, we are using a mixed-effects regression analysis with average BFI in the three phases as the outcome, phase as the within-subjects factor, and group (RA, SA, standard of care) as the primary between-subjects factor. The baseline BFI level will be used as a covariate. We shall further adjust the model for key demographic variables such as age and ethnicity, as well as the baseline HADS score. A *subject* random-effect will be used to account for the clustering effect within the three measurements on the same subject. Of primary interest is the group*phase interaction, the significance of which will indicate differences in extent of decrease between the arms. Post-hoc analyses of phase difference within each arm will be carried out multiple comparison adjustment. Model diagnostics will be carried out to confirm the distributional assumptions and appropriate corrective actions (e.g. transformation) will be performed as needed.

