Along with numerous strengths our study also has several limitations including inability to double blind the study and lack of an objective measure of fatigue. Currently, there are no biomarkers for measuring fatigue. Consequently, fatigue is measured using subjective questionnaires only. While fatigue is a subjective experience, the presence of high amounts of variability between and within participants’ fatigue, over even a short time frame of a day, argue the benefit of pairing objective measures of fatigue with subjective questionnaires. We have included the objective measurement of physical activity and sleep measures using actigraphy. While actigraphy data does not give an objective measure of fatigue it does give insights into the effect of fatigue on daily activity and sleep. Another limitation is our inability to double-blind the participants as to study assignment. Data from our pilot study
[13] demonstrated that participants were blinded as to the acupressure treatment to which they were randomized. However, this is not the case between women in this study who are randomized to one of the two acupressure arms and the standard of care arm. Despite this limitation, it is an important study design to be able to compare acupressure treatment to standard of care for fatigue in these women. By having this comparison we will be able to have a preliminary idea about the comparative effectiveness of acupressure compared to standard of care and have a clearer idea of what is the placebo versus the real effect of acupressure treatment.

In summary, this is a protocol examining two opposing types of self-administered acupressure (stimulating and relaxing) compared to standard of care for PCRF in 300 BC survivors. This protocol has many strengths compared to the traditional randomized, double-blind design. In particular, it utilizes local community resources in the form of MSU County Extension Services for study visits, population-based recruiting via the MTR, and nurses to teach the acupressure intervention. This study is scheduled to be completed with recruitment in the Winter of 2014 with published results in 2015.

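### The stated power inputs give about 0.73, not 0.82, for the group-by-phase interaction at 100 per arm

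*Protocol article*

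**What the plan says.** The section Statistics and power analysis sets out a mixed model for phase-averaged BFI with three phases (weeks 1-3, 4-6 and 7-10), three arms and a random subject effect. It then says: "Of primary interest is the group*phase interaction".

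The Power analysis section simulates a smaller model, with "a between-subject factor group (3 levels), a within-subject factor phase (2 levels), group*phase interaction and a random subject effect". For standard care, SA and RA, the assumed mean BFI is 4, 3, 3 at mid-treatment and 4, 3, 2 at end-treatment. Two variances of 4 are given: one is labelled between-subject, the other belongs to the random subject effect, and together they are said to yield an intra-class correlation of 0.5. The results are power above 0.95 for the group effect, and for the interaction: "the power for detecting a significant phase*group interaction is 0.82 with a sample size of 100 per treatment arm". The section also says: "All power calculations are carried out on the basis of 100 simulations in the software PASS 2008". It goes on to conclude that 100 women per group is more than enough to detect a fatigue difference.

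On sample size, the randomisation section describes allocation to "RA, SA or standard of care in a 1:1:1 ratio for a target total of 375 patients", which is 125 per arm. The closing summary of the Discussion describes two types of acupressure "compared to standard of care for PCRF in 300 BC survivors".

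**The concern.** The interaction power can be checked directly from the stated inputs, without simulation, and it does not come out at 0.82. This matters because the figure supports the sample size for the effect that the plan puts first. At 100 per arm, the chance of missing the assumed pattern under the two-phase model is about 27% (1 - 0.73), against the 18% (1 - 0.82) that the text implies. The conclusion that fatigue is more than adequately powered at 100 per arm then holds for the group effect but not for the interaction.

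**Working it through.** **Inputs, all from the Power analysis section.** Means are 4, 3, 3 (mid-treatment) and 4, 3, 2 (end-treatment), so the changes are d = 0, 0, -1. The subject variance is 4 and the intra-class correlation 0.5. Then 4/(4 + residual) = 0.5, so the residual variance is 4. The other variance of 4 must therefore be the residual, although it is labelled between-subject. n = 100 per arm, alpha = 0.05.

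**Check of this variance reading against the group effect.** The arm means over the two phases are 4, 3, 2.5, and their squared deviations sum to 1.167. The variance of a subject's two-phase mean is 4 + 4/2 = 6. The noncentrality is 100 × 1.167/6 = 19.4, and the F(2, 297) power is 0.98. This agrees with the stated figure of more than 0.95.

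**Two-phase interaction.** With two phases, the interaction test is a one-way F test on each woman's change.
- Variance of change = 2 × 4 = 8.
- Mean change = -1/3. Sum of squared deviations = (1/3)² + (1/3)² + (2/3)² = 2/3.
- Noncentrality = 100 × (2/3)/8 = 8.33.
- F(2, 297) power = **0.732**. A check with 40,000 simulated trials gave 0.733.

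**Three-phase interaction (the planned model).** Adding the plan's washout means of 5, 4, 3, the squared interaction terms sum to 4/9. The noncentrality is 100 × (4/9)/4 = 11.1, and the F(4, 594) power is **0.763**.

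| Analysed per arm | Two-phase | Three-phase |
|---|---|---|
| 100 | 0.732 | 0.763 |
| 125 | 0.829 | 0.861 |

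Power of 0.82 is first reached at 123 per arm with two phases and at 114 with three.

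**Can another reading give 0.82 at 100 per arm?**
- Total variance 4 with correlation 0.5 (change variance 4) gives 0.962. It also contradicts a subject variance of 4.
- The stated test would need a change variance of about 6.5 instead of 8, which nothing in the text supports.
- A 10% level gives 0.825, a 1-df contrast of RA against the mean of the other two arms gives 0.821, and a one-sided RA-SA comparison of change gives 0.804. None of these is the stated test.

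**Simulation error.** With 100 runs and true power 0.732, the standard error is √(0.732 × 0.268/100) = 0.044. The exact 95% interval for 82/100 is 0.731 to 0.890, whose lower end is just below 0.732. The probability of 82 or more successes when true power is 0.732 is 0.026; the two-sided exact p-value is about 0.054.

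**The case against.** The strongest defence is that the section discloses its method. A run of 100 simulations can return 82 when the truth is 73, and the exact interval just includes 0.73. That explains the figure, but it leaves it inaccurate: an exact value is available, and the stated inputs fix it at 0.73.

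Three further points stand and limit the consequence. First, simulating two phases instead of three is mildly conservative here (0.73 against 0.76), so the simplification does not inflate the figure. Second, at the randomisation target of 125 per arm, power is above 0.82 under either model. Third, the group effect has power of 0.98 at 100 per arm, so the comparison of overall fatigue between arms is not in doubt.

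A reader might infer that 100 per arm is the planned evaluable number, that the step from 100 to 125 is a 20% loss allowance (375 × 0.8 = 300), and that loss to follow-up is therefore not covered. The document does not support this. It states no loss rate, does not call 100 per arm the evaluable number and does not say how 375 was derived; an article may leave that to the full protocol. A reader might also conclude that about 122 per arm are needed to reach 0.82. That holds only for the two-phase simulation model, since the planned model needs about 114. In addition, BFI is collected weekly and averaged within phases in a mixed model, so a woman with some missing weeks or a missing phase can still contribute.

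**Conclusion.** The stated power for the effect of primary interest is wrong as written. On the plan's own inputs it is about 0.73 at 100 per arm, 9 points below the stated 0.82, or about 0.76 under the planned three-phase model. The most likely cause is a high estimate from too few simulations. The result assumes a residual variance of 4, which the stated correlation requires and the group-effect figure supports, together with complete data on the number analysed, equal arms and a 5% F test. The three-phase value also assumes the plan's washout means and the same correlation between every pair of phases.

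This is an error in the reported figure and in the conclusion drawn from it. It does not show that the trial is too small: if all 375 are analysed, power is about 0.83 or 0.86.

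**What to change.** 1. Recompute the interaction power from the non-central F distribution, or with at least 10,000 simulations, using the three-phase model of the analysis section. Report about 0.73 (two-phase) or 0.76 (three-phase) at 100 per arm, and about 0.83 or 0.86 if all 125 per arm are analysed.
2. Relabel the first variance of 4 as the residual (within-subject) variance.
3. Limit the statement that 100 per group is more than enough for fatigue to the group effect, and give the interaction its own figure.
4. If the 375 target includes a loss allowance over 100 per arm, state it as an assumption. The document gives none at present.

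The cost is a short recalculation and a less favourable figure at 100 per arm. Recruitment and the analysis do not change.

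### The PSQI power statement rests on a mid-treatment PSQI that is never collected and on an unstated SD, so the >99% phase and group*phase power does not apply to the planned data

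*Protocol article*

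**What the plan says.** In the protocol article's Power analysis, the sleep calculation takes two time points. At the first, "The mean PSQI values at mid-treatment are assumed to be 7, 6, 6, respectively in standard care, SA and RA arms"; at the second, "whereas the means are taken to be 7, 6, 5 at the end-treatment point in the same arms". The conclusion is: "Assuming an intra-subject correlation of 0.5, we have powers above 99% to detect any of the group, phase, and group*phase interaction effects". That figure is given for 100 women in each arm and a 5% level. No PSQI standard deviation is stated. The only spread appears just before, where "the mean PSQI in BC patients ranges from 6.84 ± 0.376 to 7.16 ± 0.325", without saying whether the ± figures are SDs or standard errors. The same section treats a 1-point fall in PSQI as clinically significant and calls the study sufficiently powered for key sleep measures.

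On data collection, Statistics and power analysis (secondary aim 1) refers to "the PSQI, which shall be administered at baseline, week 6 and week 10". Table 2 marks the PSQI at screening, week 6 and week 10. The week-3 visit and the weekly calls carry the BFI and no PSQI. The planned PSQI model follows the BFI model, which has baseline as a covariate, but with phase replaced by a continuous week variable.

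**The concern.** The powered design and the planned data do not match. A mid-treatment to end-treatment phase effect, and its interaction with group, need a PSQI during the first half of treatment, which the BFI analysis defines as weeks 1 to 3. None is scheduled, and phase is not a term in the planned PSQI model.

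The figure is also hard to reconcile with the BFI calculation next to it. Both use 100 per arm, a 5% level, a correlation of 0.5 and the same pattern of mean differences, yet interaction power is 0.82 for BFI and above 0.99 for PSQI. Only a clearly smaller PSQI spread could produce that, and none is stated.

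At stake is how the sleep results are read. The study hypothesis is that RA improves sleep quality compared with both SA and standard of care. A blanket claim of near-certain power could lead a null RA versus SA result to be taken as stronger evidence than it is.

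**Working it through.** **1. Time points.**

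| Source | PSQI times |
|---|---|
| Power analysis | mid-treatment, end-treatment |
| Statistics and power analysis | baseline, week 6, week 10 |
| Table 2 | screening, week 6, week 10 |

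The mid-treatment label cannot be a slip for baseline, because the assumed means already differ between randomised arms (7, 6, 6). Only end-treatment (week 6) is common to both.

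**2. Inputs for the power check.** Means 7, 6, 6 and 7, 6, 5 (standard care, SA, RA), correlation 0.5, n = 100 per arm, alpha 5%. The SD is not given and is treated as unknown.

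**3. Formulas** (3 groups × 2 phases, compound symmetry, noncentral F, 297 error df). With correlation 0.5, Var(end − mid) = 2·SD²·(1 − 0.5) = SD², and Var(subject mean) = SD²·(1 + 0.5)/2 = 0.75·SD².

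- Interaction: changes are 0, 0, −1, with mean −1/3 and sum of squared deviations 2/3. Noncentrality = 100 × (2/3)/SD² = 66.7/SD².
- Phase: noncentrality = 300 × (1/3)²/SD² = 33.3/SD².
- Group: arm means are 7, 6, 5.5, with sum of squared deviations 1.167. Noncentrality = 100 × 1.167/(0.75·SD²) = 155.6/SD².

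**4. Reproducing the stated figure.** With 0.325 or 0.376 entered as the SD, all three powers are 1.00, so >99% is reproduced. The article does not say that these values were used.

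**5. Largest SD that still gives 99% power.** Group 2.68, interaction 1.76, phase 1.34. All three exceed 99% only if the SD is at most about 1.34.

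| Assumed SD | Group | Phase | Interaction |
|---|---|---|---|
| 2.0 | >0.99 | 0.82 | 0.96 |
| 2.5 | 0.996 | 0.63 | 0.84 |
| 3.0 | 0.97 | 0.48 | 0.68 |
| 3.5 | 0.90 | 0.38 | 0.54 |
| 4.0 | 0.80 | 0.30 | 0.43 |

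Simulation with 4,000 replicates agreed with these formulas at the SDs tried (for example 0.966 for interaction at SD 2 and 0.546 at SD 3.5).

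**6. Comparison with BFI.** The BFI variances (4 and 4) imply a total SD of √8 = 2.83, or 2.0 if 4 is the total. The same formula gives interaction power 0.73 and 0.96 respectively; the article states 0.82. With 100 simulations, the 95% interval around 0.82 is 0.73 to 0.89. PSQI power above 99% for all three effects needs an SD well below either BFI value.

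**7. The ± figures.** If PSQI totals are whole numbers (an assumption), the smallest possible SD at a mean of 6.84 or 7.16 is √(0.84 × 0.16) = 0.367. Then 0.325 could not be an SD and 0.376 would be at the floor. Read as standard errors from assumed samples of 50 to 150, they imply SDs of about 2.3 to 4.6.

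**8. Power where PSQI is collected.** Week 6, means 7, 6, 5, 100 per arm. The three-arm test has noncentrality 100 × 2/SD²; pairwise contrasts use the noncentral t. The last row replaces SD by SD·√(1 − 0.5²), for an assumed baseline correlation of 0.5.

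| Contrast at week 6 | SD 2.5 | SD 3 | SD 3.5 | SD 4 |
|---|---|---|---|---|
| Three-arm F-test | >0.99 | 0.99 | 0.96 | 0.89 |
| RA vs standard care, 2 points | >0.99 | 0.997 | 0.98 | 0.94 |
| 1 point, e.g. RA vs SA | 0.80 | 0.65 | 0.52 | 0.42 |
| 1 point, baseline-adjusted | 0.90 | 0.77 | 0.64 | 0.53 |

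**The case against.** The strongest reply is that sleep is a secondary aim, the trial was sized on BFI, and the stated week-6 means do support good power for the broad questions. That stands. The group effect keeps 99% power up to an SD of 2.68, the week-6 three-arm test has 0.96 at SD 3.5, and RA versus standard care has 0.94 even at SD 4. Baseline adjustment, which the planned model includes, also raises the 1-point power. The randomised target of 375 would give 125 per arm, although the Discussion speaks of 300. A reader might infer that the study is underpowered for sleep as a whole; these figures do not support that.

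A second reply is that a condensed article may leave the SD to the full protocol. That is fair as to the omission. It does not explain the mid-treatment time point, which the article's own schedule contradicts.

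Two further inferences should be resisted. One is that the ± figures are certainly standard errors that were fed into the simulation. Their sources are not shown, and the article does not say what SD was used. The other is that SDs this small are ruled out by the quoted 51% with sleep disruption and 19% with insomnia. With those means and SDs, a normal distribution puts about 34% to 69% of women above 7, and neither percentage is defined there by a PSQI cut-off.

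**Conclusion.** The point holds in two parts. First, without any assumption, the >99% phase and group*phase powers refer to a mid-treatment PSQI that is not collected and to a factor that the planned PSQI model does not contain. Second, the claim of >99% for any of the three effects needs a total SD of at most about 1.34, below the 2.0 to 2.83 implied for BFI, and no PSQI SD is stated to support it.

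The second part depends on the unknown SD, so the results are shown as a range; which SD is plausible is an assumption. The ± 0.325 to 0.376 may be standard errors, but that remains an inference. The practical shortfall is confined to 1-point contrasts such as RA versus SA: 0.80 down to 0.42 unadjusted for SDs of 2.5 to 4, or about 0.90 to 0.53 with an assumed baseline correlation of 0.5. The overall arm comparison and RA versus standard care remain well powered under the stated means.

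**What to change.** Delete the mid-treatment PSQI scenario and the claim of >99% for any effect. State an individual-level PSQI SD, labelled as such and sourced, and say whether the ± figures are SDs or standard errors. Recompute power for the collected times (week 6 and week 10) under the planned baseline-adjusted model, giving the assumed baseline correlation. Report the three-arm test, RA versus standard care and the 1-point contrasts separately, and limit the sufficiently-powered statement to those that reach it.

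The cost is one rewritten paragraph and a less favourable figure for RA versus SA. It needs no additional patients, visits or PSQI administrations, and the BFI-based sample size does not change.
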